Some of the authors (JB, CL, NR, NK) have systematically developed a novel, internet-based GSH programme for PTSD based on TFCBT. This was developed over a number of years following Medical Research Council (MRC) guidance for the development of a complex intervention [26] with significant input from PTSD sufferers and professional stakeholders. Intervention development work was completed between 2007 and 2010. A modelling phase included key stakeholders in focus groups and semi-structured interviews to inform the content, delivery and guidance of a GSH programme for PTSD. Data was analysed using qualitative methodology and used to inform the first prototype. The prototype was piloted twice with a total of 19 participants with PTSD and refined on the basis of qualitative and quantitative results. Quantitative results strongly supported the potential of the programme to effectively treat PTSD [27].

An interactive online version of the programme was produced through a Knowledge Transfer Partnership (KTP) between Health Care Learning Limited Ltd (HCL) and Cardiff University. The partnership combined HCL’s expertise in developing high quality internet-based programmes, with the academic team’s experience of developing and evaluating psychological interventions for PTSD. A pilot feasibility RCT of the intervention was completed between 2012 and 2014. Forty-two participants with mild to moderate PTSD after a single traumatic event were randomised to receive immediate GSH or delayed treatment [28].

Following GSH, PTSD sufferers’ symptoms improved by over 50% (completers only) and over 40% (intention to treat) with an average of 149 min of therapist input; effect sizes that compare favourably with those found for therapist-delivered TFPT. The treatment group had significantly lower levels of traumatic stress symptoms, depression, anxiety and functional impairment at post-treatment and one month follow-up, in comparison to the delayed treatment group, who improved to the same degree after receiving GSH for PTSD. Results of the development and pilot work indicated a strong rationale for conducting a larger scale RCT to determine whether GSH represents a treatment option that should be routinely used in the care of PTSD sufferers, as it is for depression and numerous anxiety disorders.

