## Methods/design

The design is that of a multi-centre pragmatic randomised controlled non-inferiority trial with assessors masked to treatment allocation. Individual randomisation will be used.

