#### Spring: An internet based guided self-help Programme for PTSD

Spring is an online GSH programme based on TFCBT. It uses the same principles as TFCBT but aims to reduce contact time with the therapist by providing some of the therapy content and activities in an accessible self-help format. Potential advantages include that the service user can engage in the intervention at a time and place convenient to them which may reduce drop out, and it may also reduce waiting list times as it should reduce the input time required for therapist.

The expectation is that Spring will be delivered by the same therapists delivering the TFCBT. All the therapists will receive a half day’s training from two of the authors who were involved in developing the intervention and delivering it in the pilot study (NK, NR). Therapists also receive ongoing supervision of one or more training cases until they are regarded as competent. The therapists will work from a manual and, for the duration of the trial, will receive supervision once per month from NK or NR.

Spring is an 8 week online program comprising eight steps (see Table 2. Spring PTSD Steps).

**Table 2 Tab2:** Spring PTSD Steps

Step 1: Learning About My PTSD – Psychoeducation about PTSD illustrated by four actors describing their experience of PTSD to different types of traumatic event.
Step 2: Grounding Myself - Explanation of grounding and its uses along with descriptions and demonstrations of grounding exercises.
Step 3: Managing My Anxiety – Education about relaxation techniques with learning through videos of a controlled breathing technique, deep muscular relaxation and relaxation through imagery.
Step 4: Reclaiming My Life – Behavioural re-activation to help individuals return to previously undertaken/new activities.
Step 5: Coming to Terms with My Trauma – Provides rationale for imaginal exposure, narratives of the four video characters. The therapist helps the participant to begin writing a narrative, which they complete remotely and read every day for at least 30 min.
Step 6: Changing My Thoughts – Cognitive techniques to address PTSD symptoms.
Step 7: Overcoming My Avoidance – Graded real life exposure work.
Step 8: Keeping Myself Well – This session reinforces what has been learnt during the programme, provides relapse prevention measures and guidance on what to do if symptoms return.

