### Sample size

As the study aims to demonstrate non-inferiority of GSH for PTSD compared to TFCBT, the power calculation considers the non-inferiority margin as opposed to the effect size. The non-inferiority margin will be 5 points on the 80 point CAPS-5 scale. A recent meta-analysis [11] indicates that the standardised mean difference between TFCBT and waitlist/usual care for the treatment of PTSD is − 1.62. This corresponds to 16.6 points on the CAPS-5. This means that if we demonstrate non-inferiority to within 5 points of the gold standard, we will also demonstrate superiority over wait list/usual care in line with International Conference on Harmonisation Harmonised Tripartite Guideline (Statistical Principles for Clinical Trials) E9 (ICH E9) guidance for non-inferiority studies [53, 54].

Pilot work indicates an intraclass correlation coefficient of 5.6% at the therapist level at 10 weeks. At 22 weeks, however, there was no observable clustering of CAPS-5 scores amongst therapists. Given our primary outcome (CAPS-5) is measured at 16 weeks we have allowed for 1% clustering and recalculated the sample size. We have allowed for 20% attrition. On the basis of the anticipated average therapist cluster size being four, the design effect is 1.03, requiring a 3% inflation of the sample size. This results in a final sample size of 192 (inflated from 186) which provides 90% power (nQuery v7.0).

For the qualitative elements of the study, the sample size will be guided by preliminary analysis and constant comparison (comparing and contrasting themes from other interviews) during each data collection phase, until the research team is satisfied that there is data saturation and no new themes which are important to the research question arise [55]. However, it is helpful to have a guide to sample size for study planning. Based on previous research [56] we propose that interviews will be conducted with 10–20 participants and 8 therapists purposefully sampled from the different geographical sites.

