### Statistical methods

The primary analysis will be performed using analysis of covariance, predicting follow-up CAPS-5 score controlling for baseline CAPS-5 score and important patient characteristics (including all minimisation variables). This will be a complete case intention to treat analysis. Checks will be made to ensure there is no appreciable clustering of outcomes within therapists, but if such clustering exists the primary analysis will be hierarchical. The results will be summarised using point estimates, 95% confidence intervals and *p*-values. Since this is a non-inferiority design, we will be checking whether the confidence interval for the difference between arms lies entirely within the 5 point non-inferiority margin. Participants with missing CAPS-5 score at follow-up will have a CAPS-5 score estimated from available IES-R scores (this will involve building a prediction model using information from participants with both IES-R and CAPS-5 scores). We will explore differences in treatment effects by gender in a sub-group analysis by including an interaction term between treatment arm and gender.

A sensitivity analysis will use multiple imputation to account for missing data if the number of cases lost due to incomplete information exceeds 10%. Secondary outcomes include: CAPS-5 at 52 weeks, IES-R, WSAS, PHQ-9, GAD-7, AUDIT-O, MSPSS, EQ-5D, ISI, GSES, PTCI, adapted CSSRI-EU and CSQ-8. These are all continuous measures and will be analysed similarly to the primary outcome. Transformations will be explored to improve model fit if distributional assumptions are not satisfied. This will be assessed by visual inspection and formal fit statistics compared to decide on the transformation chosen.

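### The stated missing-data check is multiple imputation above 10% loss, which cannot show whether non-inferiority survives if unobserved GSH outcomes were worse than predicted

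*Protocol article*

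**What the plan says.** The protocol article describes the trial thus: "The design is that of a multi-centre pragmatic randomised controlled non-inferiority trial with assessors masked to treatment allocation" (Methods/design). On the margin, the Sample size section says: "The non-inferiority margin will be 5 points on the 80 point CAPS-5 scale". The same section says: "We have allowed for 20% attrition".

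The Statistical methods section makes the primary analysis an ANCOVA of follow-up CAPS-5 on baseline CAPS-5 and patient characteristics, including the minimisation variables. It adds: "This will be a complete case intention to treat analysis". It also says that a missing follow-up CAPS-5 score will be estimated from available IES-R scores, using a model built on participants who have both measures. Non-inferiority is judged by whether the confidence interval (95% intervals are reported) stays inside the 5-point margin.

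On robustness to missing data it says: "A sensitivity analysis will use multiple imputation to account for missing data if the number of cases lost due to incomplete information exceeds 10" per cent. The same sentence is repeated for the IES-R trajectory model. The only other sensitivity analysis in the section is a complier-adjusted causal effect (CACE) analysis, which concerns adherence and not missing outcomes.

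**The concern.** In a non-inferiority trial, missing outcomes can favour the new treatment. If people lost from GSH did worse than the retained data predict, and this is not matched in TFCBT, the estimated difference moves towards non-inferiority. A sensitivity analysis is useful here only if it can show how bad the unseen outcomes would have to be before the verdict changes.

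The stated check does not do that. Complete-case ANCOVA assumes that lost and retained participants with the same covariates have the same expected outcome. Ordinary multiple imputation assumes the same, given whatever is in the imputation model. With only the outcome missing and the same covariates, it essentially returns the complete-case estimate. Adding IES-R weakens the assumption, because deterioration recorded before loss then enters the imputation. What happens after the last IES-R score stays untested. IES-R is also likely to be sparser in GSH: the Outcomes section expects fortnightly collection there, against weekly in TFCBT.

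The trigger is a second, smaller weakness. It counts cases overall, so a modest total can hide heavy loss in one arm.

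**Working it through.** **Inputs**
- Margin 5 points, planned loss 20%, design effect 1.03, total 192 (Sample size). The 1:1 ratio (Allocation and blinding) gives 96 per arm.
- SD: not stated. The Sample size section says that a meta-analysis "indicates that the standardised mean difference between TFCBT and waitlist/usual care for the treatment of PTSD is − 1.62", and equates this to 16.6 CAPS-5 points. Implied SD = 16.6 / 1.62 = 10.25.
- Delta (how many points worse lost participants are than a missing-at-random analysis predicts), the observed differences and any split of loss between arms are assumptions, shown as ranges.

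**The plan's own figure**

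With SD 10.25, margin 5, no true difference, 90% power and one-sided 5%, the t-based formula gives 73 per arm. Then 146 / 0.8 = 182.5, or 184 when rounded up by arm, and 184 × 1.03 = 189.5. This is within 3% of the stated 186 and 192 (186 × 1.03 = 191.6), so the implied SD is a fair working value. At one-sided 2.5%, which matches a 95% interval, the same steps give 231 to 233. Under that rule 192 gives about 85% power. The calculations below use the 95% interval, as the Statistical methods section does.

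**Tipping point at the planned loss**

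Observed per arm = 96 × 0.8 = 76.8.

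SE = 10.25 × √(1.03 × (1/76.8 + 1/76.8)) = 1.68; 1.96 × SE = 3.29.

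If only GSH outcomes depart from prediction, the full-sample difference rises by (GSH loss fraction) × delta. Hence tipping delta = (5 − upper limit) / GSH loss fraction.

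| Observed difference | Upper 95% limit | Room to 5 | Tipping delta |
|---|---|---|---|
| 0 | 3.29 | 1.71 | 1.71 / 0.20 = about 8.5 |
| 1 | 4.29 | 0.71 | 0.71 / 0.20 = about 3.5 |
| 1.5 | 4.79 | 0.21 | 0.21 / 0.20 = about 1 |

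**Chance of a false verdict**

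With a true difference of 5 and 20% loss per arm, the chance of declaring non-inferiority is Φ(0.20 × delta / 1.68 − 1.96). This gives 2.5%, 4.8%, 8.6% and 22.1% at delta 0, 2.5, 5 and 10. More generally the shift is (GSH loss × GSH delta) − (TFCBT loss × TFCBT delta), so equal loss with equal deltas gives no bias.

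**The 10% trigger**

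19 / 192 = 9.9%, so no imputation is run. If all 19 are in GSH, that arm has lost 19 / 96 = 19.8%.

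SE = 10.25 × √(1.03 × (1/77 + 1/96)) = 1.59. The upper limits are 3.12, 4.12 and 4.62, and the tipping deltas about 9.5, 4.5 and 1.9.

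With 10% lost evenly in each arm, which also does not exceed the trigger, SE = 1.58 and the tipping deltas are about 19, 9 and 4.

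**The case against.** The strongest objection is that this is a condensed article. It does not say that multiple imputation is the only check, never uses the term missing at random, and gives no imputation model. A delta-adjusted imputation would fit its sentence, and the full analysis plan may contain one. That stands as a limit on the claim: the point is about what the article fixes, on its ordinary reading. But the article is not silent. It names the method and a numerical trigger, and the trigger as written permits no check at or below 10% loss.

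Second, IES-R is collected partly to support imputation, so some deterioration would be seen. That also stands. Delta here means only the part of the deficit that the observed data do not predict.

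Third, the trigger will probably be met, since 20% attrition is planned. Agreed; it is the lesser fault.

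Three stronger readings are tempting but unsupported:
- **The pilot shows that lost participants did not improve.** The Background reports that GSH "symptoms improved by over 50% (completers only) and over 40% (intention to treat". Setting 0.8 × 50 + 0.2 × d = 40 gives d = 0, but the 20% is this trial's planned loss, not the pilot's. With 10%, 30% or 40% loss the same equation gives d = −50, about +17 or +25. The percentages are lower bounds, and the article gives neither the pilot's loss nor its intention-to-treat method.
- **The protocol expects outcome loss to differ by arm.** The remarks that drop-out from trauma-focused therapy can be high (Background) and that GSH can be used at a time and place "convenient to them which may reduce drop out" concern leaving therapy. Under Participant withdrawal, those who leave only the intervention stay in follow-up. The data collection section adds tracing, vouchers and CAPS-5 as a minimum dataset.
- **GSH will lose more people than TFCBT.** No passage supports this. If the drop-out remarks did carry over to outcomes, they would point the other way.

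**Conclusion.** The concern holds in a limited form, as a cheap improvement. The missing-data check that the article states cannot test outcomes worse than the observed data predict, and neither the IES-R prediction nor the CACE analysis fills that gap. At the planned loss the verdict is fairly sturdy if the arms look equal (tipping delta about 8.5 points) but fragile if GSH looks 1 to 1.5 points worse (about 3.5 down to 1 point).

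These sizes rest on the implied SD of 10.25, a 95% interval, 20% loss in each arm, TFCBT outcomes as predicted, and no precision gain from baseline adjustment. They show what the planned check could not reveal. They are not evidence that lost GSH participants will do worse, nor that a non-inferiority result from this trial would be wrong.

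**What to change.** In the Statistical methods section, remove the 10% trigger for the primary outcome and always run multiple imputation for CAPS-5 at 16 weeks, using baseline CAPS-5, arm, the minimisation factors and IES-R. Add a delta adjustment to the imputed scores, varied separately by arm over a range fixed in advance. Report the delta at which the upper 95% limit crosses 5 points. A range reaching about 10 points would contain all the tipping points found above for the planned 20% loss.

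Do not attach a pass/fail rule, such as requiring the verdict to survive a 5-point penalty. The margin is a difference between arm means, not a deficit per missing person. At 20% loss a 5-point penalty moves the estimate by 0.20 × 5 = 1.0 point. With truly equal arms and data missing at random, the chance of passing would fall from Φ(5/1.68 − 1.96), about 85%, to Φ(4/1.68 − 1.96), about 66%. Report the tipping point and let readers judge how plausible it is.

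The cost is a change of wording and a few more model runs, with no new participants, visits or data. The downside is that a non-inferiority claim may have to be reported as sensitive to missing data.

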### Health economics

An economic evaluation will be conducted from the perspective of the UK NHS and personal, social services. To determine the cost-effectiveness of GSH versus CBT for PTSD, and the extent to which it can be regarded as representing value for money, two analyses will be undertaken – one will assess the relative cost-effectiveness by estimating the incremental costs of achieving changes in natural units of outcome that commissioners, health care professionals, public health decision makers and service users find relevant (e.g. incremental cost of achieving a percentage improvement in PTSD symptoms as measured by CAPS5). The second analysis will use the EQ-5D utilities for a cost utility analysis estimating the incremental costs per quality adjusted life year (QALY) gained. The QALY gains will also be used in a net–benefit analysis based on accepted NICE ‘value for money’ thresholds.

The contributions associated with the GSH in relation to staff time and costs associated with training of therapists, along with materials and equipment used in the process associated with GSH development and implementation, will be collected during the trial by interviews with relevant finance staff, logged in physical units and translated into costs using published unit costs [e.g. [63, 64]. Resource utilisation of services prior to the GSH implementation, as a result of the intervention, and at follow-up relative to the control group, will be measured using the CSSRI-EU.

As the follow-up is at 52 weeks, no costs and outcomes will be subjected to discounting. Uncertainty around the cost and effectiveness estimates will be investigated by: probabilistic sensitivity analysis, using the incremental cost per QALY as the metric for this assessment measured against the NICE range of ‘willingness to pay’ thresholds between £20 k and £30 k per incremental QALY gained represented by cost-effectiveness acceptability curves [65]. a series of one-way sensitivity analyses to assess the impact of parameter variation on baseline estimates of the range of incremental cost-effectiveness ratios; and a set of alternative scenarios will be constructed, based on the findings from relevant studies of CBT for PTSD [33, 35–37] to compare the relative cost-effectiveness of GSH against different durations of CBT and supportive care .

In addition to a trial-based analysis, longer-term cost-effectiveness will be assessed using decision analytic modelling methods. The derived model, based on a review of published models at the time of the analysis, will use parameter estimates derived from the trial and information from literature sources relating to long-term effects of PTSD, alongside other sources, to arrive at meaningful long-term estimates of cost-effectiveness and budget impact.

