### Dissemination

Trial findings will be disseminated widely using a variety of tailored methods targeting specific audiences. A summary report of trial results written in lay language will be sent to study participants and other key stakeholders. The report will also be displayed and available at venues used for recruitment. We will hold informal patient-centred meetings at each trial site, to present the results orally and allow time for questions and clarification. We will also hold an open conference at each centre in the final month of the project. If the outcome is positive, the conferences will include free training in the GSH programme for NHS staff coupled with free access to the programme for a certain number of therapeutic encounters. We will send reports of trial results to NHS commissioners, outlining the cost-saving potential of GSH if applicable and the scope for improving routine clinical practice for PTSD. We will disseminate the findings publicly through news items on the NCMH website (www.ncmh.info), which attracts an average of 2250 unique visitors each month, and an article in the widely circulated NCMH newsletter.

We will publicise the trial results through social media and publish posts related to trial progress and results on the NCMH blog-site. This site features posts that have attracted up to 10,000 hits. We have experience of successfully engaging local and national media and will work with the NCMH communications team to formulate strategies for press releases and the dissemination of findings through newspaper articles and radio features. We will work with knowledge brokers, such as the Science Media Centre, to maximise coverage. Study outcomes will be presented to the academic community at national and international conferences by means of oral presentation, poster presentation, and interactive workshops. We will target conferences likely to be attended by large numbers of therapists and managers working in IAPT and other primary and secondary care NHS psychological treatment services. We will also disseminate to the third sector and other services likely to deal with individuals with PTSD who could potentially benefit from treatment (e.g. SARCs, Victim Support). We aim to publish the quantitative, qualitative and health economic results in high impact, open-access, peer reviewed journals. A complete account of the research will also be published in the NIHR HTA Journal.

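### Under an NHS and personal social services perspective, the plan costs resources used to develop GSH, although the programme was built before this trial and those resources are sunk

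*Protocol article*

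**What the plan says.** All references are to the protocol article.

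- **Perspective** (Health economics): "An economic evaluation will be conducted from the perspective of the UK NHS and personal, social services".
- **Resources costed for GSH** (Health economics): staff time and therapist training, "along with materials and equipment used in the process associated with GSH development and implementation". They are gathered during the trial through interviews with finance staff and are "logged in physical units and translated into costs using published unit costs".
- **History of the programme** (Background): "Intervention development work was completed between 2007 and 2010". An online version was then made jointly by the university and a company, and a pilot randomised trial ran from 2012 to 2014. The trial registration section dates this trial's registration to December 2016.
- **Use of the result**: the Health economics section plans a cost per unit of clinical outcome, a cost per QALY, a net-benefit analysis, and a longer-term model with budget impact. The Dissemination section says commissioners will be told of any cost-saving potential.
- **Access after the trial** (Dissemination): if the result is positive, NHS staff get free training and "free access to the programme for a certain number of therapeutic encounters".

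**The concern.** An evaluation from the payer's side, meant to inform a decision to adopt, should count what the payer would spend or save by adopting. Money already spent on building a programme is the same whether or not the NHS takes it up, so it does not belong in the incremental cost. The article names development and implementation side by side as costed items and does not treat them differently.

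The cost side may carry much of the economic conclusion. The trial tests non-inferiority, so a small QALY difference between arms is plausible, and net benefit would then turn mainly on the cost difference. An item that burdens only the GSH arm, and that no adopting service would pay, would make GSH look dearer than it is. The planned one-way sensitivity analyses vary parameters around the baseline estimate. They do not by themselves remove an item that should not be in it. The longer-term model draws parameters from the trial, so the item could carry over into the budget impact.

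**Working it through.** The article contains no cost figure, so there is no stated result to reproduce. The check sets the sections side by side, then asks whether a size can be given.

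**1. Is development in the costing?** Yes, on the wording. The Health economics sentence names it as a purpose for which materials and equipment were used, next to implementation, and says the items in that sentence will be translated into costs. No clause sets it apart or reserves it for a secondary analysis.

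**2. Was that development finished before the trial?** Yes, for the main work. The Background dates development work to 2007 to 2010. The production of the online version is not dated, but the account places it before the 2012 to 2014 pilot, and the abstract describes the piloted programme as online. The trial was registered in December 2016.

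**3. Would an adopting service pay it again?** Nothing in the article suggests so. The programme exists. A service would face therapist time, training, materials and possibly an access charge.

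**4. Direction.** The item attaches to GSH alone, so counting it raises the incremental cost of GSH.

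**5. Size.** This would need a development cost F and a rule for dividing it, and the article gives neither. The following is illustration only.

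- GSH participants: 192 at 1:1 (Sample size; Allocation and blinding), so 192 / 2 = 96.
- If F were divided over those 96 (an assumption, not a rule in the plan), the addition per participant is F / 96:
  - F = £10,000: £104
  - F = £50,000: £521
  - F = £100,000: £1,042
  - F = £250,000: £2,604
- If F were divided over an assumed 1,000 users, the same £10,000 to £250,000 gives £10 to £250.

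For scale, compare planned therapist contact (Interventions):

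- TFCBT, at the maximum of 12 sessions: 12 × 60 = 720 to 12 × 90 = 1,080 min.
- GSH: 60 + 4 × 30 = 180 min, plus four brief contacts. At an assumed 0 to 20 min each, that is 180 to 260 min.
- Difference: 720 − 260 = 460 min (7.7 h) to 1,080 − 180 = 900 min (15 h). Fewer TFCBT sessions would shrink it.
- At an assumed £50 per therapist hour: 460 / 60 × 50 = £383 to 15 × 50 = £750 per participant.
- The F that would cancel this over 96 participants: 96 × £383.33 = £36,800 to 96 × £750 = £72,000. At an assumed £30 to £100 per hour the range widens to 96 × 7.667 × 30 = about £22,000 to 96 × 15 × 100 = £144,000.

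The addition could therefore be trivial or could exceed the whole saving in contact time. Which of these applies depends on figures that the article does not give.

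**The case against.** **The clause may mean something narrower.** In the sentence, development qualifies materials and equipment, not the whole multi-year programme. The data are to be collected during the trial from finance staff, which fits local set-up better than recovering the cost of prototype work from 2007 to 2010. The sentence also says the items will be collected and costed, without saying that development enters the base-case increment. All of this is fair, and it is why the fix offers a rewording. It does not remove the point, because the article sets development beside implementation and then costs both without distinction.

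**Other analyses could handle it.** Scenario analyses and a decision model using outside sources are planned, and neither is barred from leaving development out. But the text does not say that they will, and the trial-based estimate would still contain it.

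Three stronger readings are tempting, and the documents do not support them.

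- *A reader might infer that one-off costs such as training will be spread over about two GSH participants per therapist.* The count follows from the Sample size section: 192 / 4 = 48 therapists, and 96 / 48 = 2 if the same therapists serve both arms. That is a design-effect assumption and not a costing rule. The article states no allocation base, and a condensed article may leave that to the full plan.
- *A reader might infer that an access charge has been left out.* Free access for a limited number of encounters suggests that access may later be charged, but no fee or price is stated, and materials for implementation could cover one.
- *A reader might infer that the incremental cost is wrong.* No cost has been reported, so none can be wrong. If an access charge were also left uncounted, that would favour GSH, so the net sign across both matters is unknown.

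**Conclusion.** The point stands in a limited form. Read as written, the plan puts resources spent on developing GSH into a costing done from the NHS and personal social services perspective, although the article's own history shows the programme was built and online before the trial. Those costs are sunk for the decision at hand, and counting them would bias the incremental cost against GSH.

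The direction of this one item is clear. Its size cannot be computed from the document, and the pound figures above rest wholly on assumed development costs, hourly rates and a simple division over participants. The conclusion assumes that development carries its ordinary meaning of creating the programme. If it means setting up the service locally during the trial, the fault is one of wording only.

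**What to change.** In the Health economics section:

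1. Restrict the base-case GSH cost to implementation and delivery: therapist time, training, materials, and any access charge that a service would pay. Because no price is stated, give the access charge a sensitivity range that includes zero.
2. Report development resources separately, outside the incremental cost.
3. If development was meant as local set-up during the trial, replace the word with that description and keep the item.

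The cost is a few sentences in the health economics plan and one enquiry to the programme's owner about price. Trial conduct and the clinical analysis are unaffected, and anyone interested in development spending would still find it reported.
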